### Interventions

Patients considered eligible and who have signed a written informed consent are randomly assigned to one of the two treatment arms in a 1:1 ratio. Eligible patients will be stratified according to age (≤75 versus > 75 years), ECOG PS (0–1 versus 2) and G8 Score (≤14 versus > 14).

#### Arm A: FOLFOX plus panitumumab

Patients randomized to this arm receive FOLFOX-panitumumab every 2 weeks up to 12 cycles with the following schedule:Panitumumab 6 mg/kg iv over 60 min, day 1; if the first infusion is tolerated, then subsequent infusions may be administered over 30 to 60 min;Oxaliplatin 85 mg/sqm iv over 2 h, day 1;L-Leucovorin 200 mg/sqm iv over 2 h, day 1;5-fluoruracil 2400 mg/sqm 48 h-continuous infusion, starting on day 1;

If no progression occurs, patients receive maintenance panitumumab at the same dose used at the last cycle of the induction treatment. Panitumumab is repeated biweekly until disease progression, unacceptable toxicity or patient’s refusal.

#### Arm B: 5-FU/LV plus panitumumab

Patients randomized to this arm receive 5FU-panitumumab every 2 weeks up to 12 cycles with the following schedule:Panitumumab 6 mg/kg iv over 60 min, day 1; if the first infusion is tolerated, then subsequent infusions may be administered over 30 to 60 min;L-Leucovorin 200 mg/sqm iv over 2 h, day 1;5-fluoruracil 2400 mg/sqm 48 h-continuous infusion, starting on day 1;

If no progression occurs, patients receive maintenance panitumumab at the same dose used at the last cycle of the induction treatment. Panitumumab is repeated biweekly until disease progression, unacceptable toxicity or patient’s refusal.

Disease assessment is performed every 8 weeks by means of CT scan, according to RECIST 1.1 criteria.

Surgical radical resection of residual metastases in responsive patients is recommended and its feasibility should be evaluated every 2 months. After resection, patients will receive post-operative therapy up to 12 cycles of the same chemotherapy regimen plus panitumumab received before resection.

The second- and subsequent lines of treatment will be based on investigators’ choice.

### Statistical design

Assuming exponentially distributed event times, uniform accrual over time, no loss to follow-up and an expected median PFS time equal to or greater than 9.65 months with both experimental regimens, corresponding to a 6-month PFS probability ≥65%, a sample size of 90 patients in each arm will guarantee to the study a power equal to 90% for a one-sided Brookmeyer-Crowley test, with a type I error rate equal to 5%, against the null of a median PFS time equal to or less than 6 months.

The Kaplan-Meier approach will be used to estimate median PFS for each treatment arm. The hypothesis test will be conducted according to Brookmeyer-Crowley, comparing the cumulative hazard estimate at 6 months to the –log(0.50). No formal comparison between the results of the two treatment arms will be allowed.

All analyses of secondary endpoints will be descriptive only and no formal statistical comparisons will be made between the arms. Survival curves will be calculated according to Kaplan–Meier methods. Log-rank tests stratified by the same factors as used for randomization will also be performed, as well as multivariable models including all the significant baseline variables. The median event times and corresponding 2-sided 95% CI for the median will be provided.

The prognostic value of baseline G8 assessment for predicting patients’ outcome will be investigated through Cox proportional hazards model. The relationship between baseline data and patients’ survival will be graphically investigated. The prognostic value of changes of G8 score from baseline to disease progression will be similarly investigated. The analyses will be adjusted for known clinical prognostic factors. All analyses will be adjusted for multiple testing.

The association of G8 score with clinical outcome will be assessed in terms of the difference in OS in the two groups of patients (score ≤ 14 versus > 14) by means of log-rank test.

The association of CRASH score with toxicity will be assessed comparing G3–4 adverse events in the four risk categories (low, medium-low, medium-high and high risk) by means of chi-square test.

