### Study endpoints

The primary endpoint is Progression Free Survival defined as the time from randomization to the first documentation of objective disease progression or death due to any cause. Documentation of disease progressive disease is defined as per Response Evaluation Criteria in Solid Tumors (RECIST) 1.1 criteria [22] based on investigator assessment.

The secondary endpoints include OS, ORR, early tumor shrinkage (ETS), R0 Resection Rate, overall toxicity rate (OTR), Toxicity Rate and geriatric assessment by G8 and by CRASH.

OS is defined as the time from randomization to the date of death due to any cause. The objective Response Rate will be evaluated according to RECIST 1.1 based on investigator reported measurements.

Early Tumor Shrinkage Rate is defined as the percentage of patients, relative to the total of the enrolled subjects achieving a ≥ 20% decrease in the sum of diameters of RECIST target lesions at week 8 compared to baseline.

Adverse events are evaluated according to the National Cancer Institute Common Terminology Criteria for Adverse Events (NCI CTCAE) version 4.0 [23], during the induction and the maintenance phases of treatment.

Of note, this is the first trial in which the prognostic role of the G8 score will be prospectively evaluated. The assessment by G8 score is defined as the score resulting from the G8 screening tool dichotomizing patients in two groups (score ≤ 14 and > 14). Moreover, the Geriatric Assessment by CRASH score, defined as the identification of four categories of different toxicity risk (low, medium-low, medium-high, high), will be prospectively correlated with toxicity.

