### Clinical setting

Metastatic colorectal cancer patients aged ≥70 years are evaluable for the inclusion in the present study, an ECOG PS of 1 or 2 is required for patients aged 70 to 75 years, while an ECOG PS of 0 to 1 is required for patients aged more than 75 years.

Main eligibility criteria include:measurable disease according to RECIST version 1.1;centrally assessed wild-type *RAS* and *BRAF* status of primary colorectal cancer or related metastasis *(see following paragraph);*geriatric assessment by G8 screening tool and CRASH score *(see following paragraph)*;adequate bone marrow, liver, and renal function;no previous exposure to an oxaliplatin-containing adjuvant therapy. Previous adjuvant chemotherapy with fluoropyrimidines alone is allowed if more than 6 months have elapsed between the end of the adjuvant therapy and disease relapse.

Main exclusion criteria include:peripheral neuropathy of grade 1 or higher according to NCI CTCAE version 4.0;contraindications to study drugs.

Each patient’s eligibility is verified by using an electronic WEB-based system.

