### Geriatric assessment

Geriatric assessment by G8 screening tool is performed at baseline and at the time of disease progression. The G8 screening tool includes seven questions focusing on nutritional status, mobility, neuropsychological problems, medication use, self-rated health status and age. Each question provides from 2 to 4 possible answers and a score is assigned at any type of answer. The sum of the answers scores plus a score based on the age of the patient will be the final score. It ranges from 0 to 17 (Table 2).

**Table 2 Tab2:** G8 Screening Tool

	Items	Possible Answers
A	Has food intake declined over the past 3 months due to loss of appetite, digestive problems, chewing or swallowing difficulties?	0: severe reduction in food intake 1: moderate reduction in food intake 2: normal food intake
B	Weight loss during the last 3 months?	0: weight loss > 3 kg 1: does not know 2: weight loss between 1 and 3 kg 3: no weight loss
C	Mobility	0: bed or chair bound 1: able to get out of bed/chair but does not go out 2: goes out
D	Neuropsychological problems	0: severe dementia or depression 1: mild dementia or depression 2: no psychological problems
F	Body Mass Index (weight in kg/height in m2)	0: BMI less than 19 1: BMI 19 to less than 21 2: BMI 21 to less than 23 3: BMI 23 or greater
G	Takes more than 3 medications per day	0: yes 1: no
H	In comparison with other people of the same age, how does the patient consider his/her health status?	0: not as good 0,5: does not know 1: as good 2: better
I	Age	0: > 85 1: 80–85 2: < 80

The CRASH screening tool is performed only at baseline by local investigators according to the online CRASH Score Calculator developed by Moffit Cancer Center [24]. This score stratifies patients in four risk categories of severe hematologic, non-hematologic and combined toxicities.

The hematologic sub-score is calculated by the sum of scores (ranged from 0 to 2) assigned to the following items: diastolic blood pressure, IADL, LDH, and MAX2 index.

The non-hematologic score is calculated by the sum of scores (ranged from 0 to 2) assigned to the following items: ECOG PS, Mini Mental State Exam (MMSE), Mini Nutritional Assessment and MAX2 index.

The combined score is calculated by the sum of scores (ranged from 0 to 2) assigned to the following items: diastolic blood pressure, IADL, LDH, ECOG PS, MMSE, MNA and MAX2 index (Table 3).

**Table 3 Tab3:** CRASH Scoring System

Item	Score

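### The G8 change score re-scores age at progression, so passing 80 or 86 looks like a one-point decline; the effect is small, and fixing the age item at baseline removes it

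*Protocol article*

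**What the plan says.** Three statements in the protocol article combine.

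- **Score (Geriatric assessment).** "The sum of the answers scores plus a score based on the age of the patient will be the final score". The age row of Table 2 reads "0: > 85 1: 80–85 2: < 80", and of the total the text says "It ranges from 0 to 17".
- **Timing (Geriatric assessment).** "Geriatric assessment by G8 screening tool is performed at baseline and at the time of disease progression".
- **Analysis (Statistical design).** The baseline score is studied with a Cox model, and then: "The prognostic value of changes of G8 score from baseline to disease progression will be similarly investigated". On covariates: "The analyses will be adjusted for known clinical prognostic factors". The factors are not listed.

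On age at entry, Clinical setting says: "Metastatic colorectal cancer patients aged ≥70 years are evaluable for the inclusion in the present study". No upper limit is stated, so both age boundaries lie within the eligible range.

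**The concern.** The change analysis asks whether worsening geriatric status carries prognostic information. Age advances for everyone at the same rate, but the age points drop only when a boundary is passed. A patient randomized at 79 who gives the same answers at 80 therefore scores one point lower, and so does a patient who goes from 85 to 86.

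The chance of passing a boundary grows with the time between the two assessments, and that time is the time to progression. The spurious decline therefore gathers in patients whose disease was controlled longest. Where survival is counted from randomization, those patients also tend to live longer, so the artefact works against finding that decline goes with poor survival. Adjusting for baseline age would not fully remove it, because the loss depends on closeness to a boundary and on elapsed time together.

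**Working it through.** The article gives no figure for the G8 change, so there is none to reproduce. The PFS input is consistent with itself: a 9.65-month exponential median gives 6-month PFS of exp(−ln 2 × 6/9.65) = 0.650, the stated 65%.

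**1. The score.** The Table 2 maxima sum to 2+3+2+2+3+1+2+2 = 17. Age contributes 2, which leaves 15 for the seven questions. With all answers unchanged, passing 80 changes the total by 1 − 2 = −1, and passing from 85 to 86 changes it by 0 − 1 = −1. The figure 86 takes age in completed years.

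**2. Who is affected.** If the age density near a boundary is roughly flat at *f* per year, the chance of passing it before progression at time *t* is about *f·t*, proportional to PFS. For exponential PFS with median *m*, the share of crossers with above-median PFS is

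E[T; T > m] / E[T] = 0.5 × (1 + ln 2) = 84.7%.

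**3. How many: hand check.** Assume ages uniform on 70–90, so *f* = 0.05 at each of the two boundaries. Full follow-up gives 2 × 0.05 × E[T].

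- Median 6 months: E[T] = 6/ln 2 = 8.66 months = 0.72 years, so 7.2%.
- Median 9.65 months: E[T] = 13.9 months = 1.16 years, so 11.6%.

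Simulation gives the same two values.

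**4. How many: skewed ages and the study length.** The age distribution is not in the article, so it is an assumption: 70 plus a gamma variable, median 76–77. PFS is exponential as in Statistical design. Study schedule gives 24 months of accrual and a 36-month total, so follow-up runs from 12 to 36 months.

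| | Full follow-up | Progressions seen by 36 months |
|---|---|---|
| Median PFS 6 months | 5.2–6.0% | 4.0–4.7% |
| Median PFS 9.65 months | 9.1–10.2% | 5.1–5.9% |

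At 9.65 months about 80% of the 180 patients progress by the cut-off: 180 × 0.80 × 0.051 to 0.059 is about 7–8 patients. Among these progressions, 11–13% of those after 12 months are affected against 1.5–1.8% of those before 6 months, about a sevenfold gradient.

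**5. Sensitivity to the age assumption.** Across uniform ages (70–85, 70–90) and truncated normal ages (mean 76, 77 or 79, SD 4), with medians of 6 and 9.65 months, the 36-month figure runs from about 4% to 9% (about 7–13 of 180). The full follow-up figure runs from 6% to 15%. In every case 81–89% of crossers have above-median PFS.

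**6. Effect on the estimate.** This needs further assumptions. Cox simulations used a true log hazard ratio of 0.12–0.15 per point lost; some used an SD of change of 1.5 or 2.5 and age and PFS effects on or off.

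- Clock at randomization: the coefficient is 0.87–0.98 times its artefact-free value, typically a loss of 3–12%.
- Clock at progression: 0.96–1.03 times, so nearly nil and not always towards the null.
- The largest absolute shift was about 0.014 in log hazard ratio, against a standard error of roughly 0.03–0.05 with about 150 deaths.

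**The case against.** The strongest case against is that the article condenses a fuller plan. It does not say how change is coded or whether the age points are re-scored, and deriving a secondary, descriptive variable is normally left to the SAP. Age also belongs to G8, so subtracting two totals is faithful to the instrument.

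Part of this stands. The SAP may already hold age fixed, and the analysis is secondary. But the article itself states the score, the two assessment times and the analysis of change, and together these produce the artefact unless something is added. Keeping age in the baseline score is right. A birthday is still not a change in the patient's condition.

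Stronger readings are tempting and are not supported:

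- **Around one patient in ten is affected, and one in five late progressors.** Figures of that size need every patient followed to progression. Under the planned study length they roughly halve. The simulations also treat every PFS event as a progression, whereas a patient who dies without progressing has no G8 at progression.
- **Patients move across the 14-point cut.** Study endpoints describes the tool as "dichotomizing patients in two groups (score ≤ 14 and > 14"), and that cut serves stratification and the OS comparison. No section says patients are regrouped at progression.
- **The bias has a known direction whatever the analysis.** Attenuation appears with the clock at randomization. With the clock at progression, the effect is close to zero and its sign depends on how age relates to later survival. The article does not say which clock the change analysis uses.

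**Conclusion.** The point holds as a small improvement. As written, the G8 change score contains a one-point decline that reflects only passing 80 or 86, and it falls mainly on patients with long PFS. The mechanism follows from the article's own definitions, and the concentration in long PFS follows from its exponential assumption.

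The size rests on an assumed age distribution: with right-skewed ages, about 4–6% of progressions observed within 36 months, somewhat more if patients are older. The consequence is modest attenuation for survival from randomization, well inside sampling error, and almost nothing for survival from progression. The primary PFS test, the randomization strata and the baseline G8 analysis do not use the change score and are unaffected.

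**What to change.** Add one sentence to the analysis text: for the analysis of change in G8 from baseline to progression, the age points are held at their baseline value, so that change is computed from the seven answered items (0–15 points at each assessment). Report the difference in full G8 totals alongside as a sensitivity analysis. Keep the full score, age included, for stratification and for the baseline prognostic analysis.

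This sets the age-only change to exactly zero for every patient. It needs no new data: the age points follow from age at each assessment and can be subtracted from a recorded total. The one downside is a change score that differs slightly from the difference of two full G8 totals, which the sensitivity analysis makes visible.

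### G8 change to progression is to be analysed like baseline G8; read plainly, this puts a value known only at progression on a clock that starts at randomization

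*Protocol article*

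**What the plan says.** Four statements in the protocol article bear on this.

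- Statistical design, baseline score: "The prognostic value of baseline G8 assessment for predicting patients’ outcome will be investigated through Cox proportional hazards model". A graphical look at baseline data against survival follows.
- Statistical design, change score: "The prognostic value of changes of G8 score from baseline to disease progression will be similarly investigated". Adjustment for known clinical prognostic factors and for multiple testing is then promised.
- Geriatric assessment, timing: "Geriatric assessment by G8 screening tool is performed at baseline and at the time of disease progression". No visit in between is mentioned.
- Study endpoints, clock: "OS is defined as the time from randomization to the date of death due to any cause", and PFS is the "time from randomization to the first documentation of objective disease progression or death due to any cause".

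The one outcome tied to G8 by name is OS: "The association of G8 score with clinical outcome will be assessed in terms of the difference in OS in the two groups of patients", split at a score of 14. The article mentions no survival time counted from progression, no landmark, no delayed entry and no time-dependent covariate. It does not say how patients without a second G8 enter the change analysis.

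**The concern.** A Cox model from randomization suits a baseline score. A change score is different, because it does not exist until the patient progresses.

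- Every patient with a change score lived to progression, so the stretch from randomization to progression cannot contain a death.
- That stretch is also part of OS. If G8 change is related to how long progression took, covariate and outcome share a component, and an association appears even when G8 change says nothing about later survival.
- If patients without a second G8 are counted as unchanged, the reference group mixes patients still progression-free with patients who died without progressing. That adds a further bias.

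At stake is the sign and size of a published hazard ratio. A harmless decline could look protective or harmful, and a real harm could be hidden. The Discussion hopes the G8 results will support use of the tool in everyday practice.

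**Working it through.** **The plan's own figure.** The only design figure is 90% power per arm. With a median of 9.65 months, S(6) = exp(−6 × ln 2 / 9.65) = 0.650. With n = 90, one-sided 5% and the null variance, power = Φ[(0.650 − 0.50 − 1.645 × √(0.25/90)) / √(0.650 × 0.350/90)] = Φ[0.0632/0.0503] = 0.896. With the alternative variance it is 0.909. The stated figure is reproduced, and the present point does not touch it. The article gives no figure for the G8-change analysis.

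**Inputs from the article.** 180 patients (2 × 90); exponential PFS with median 9.65 months; 24 months of accrual and at least 12 months of follow-up, so a cut-off at 36 months.

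**Assumptions not in the article.** Rate of G8 decline; noise SD 2 points; median post-progression survival 12 months unless varied; no true effect of G8 change unless stated.

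**How many have a second G8.** With λ = ln 2 / 9.65 = 0.0718, the expected share with a PFS event by the cut-off is 1 − (e^(−12λ) − e^(−36λ))/(24λ) = 1 − (0.422 − 0.075)/1.724 = 0.799, or 144 of 180. If 10% of these events are deaths without progression (assumed), about 130 remain.

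**Simulation 1: points lost = drift × time to progression + noise.** Progressors only, no true effect. HR is per point lost; ranges cover repeated independent runs.

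| Drift (points/month) | Clock at randomization: HR | False positives at nominal 5% |
|---|---|---|
| 0 | 1.00 | 5–6% |
| 0.05 | 0.95 | about 16% |
| 0.1 | 0.91 | 39–43% |
| 0.2 | 0.87 | 83–86% |

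With the clock at progression, HR is about 1.00 and false positives are near 5% in every row. At 0.1 point per month, the randomization-clock rate is about 70% if median post-progression survival is 6 months and about 30% if it is 18.

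**Simulation 2: worsening yes/no, related to time to progression in either direction.** 10% of PFS events are deaths without progression; no true effect. With the clock at randomization, progressors only:

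- worsening goes with earlier progression: HR 1.24 (weaker link) or 1.50 (stronger link), false positives 15% or 38%;
- worsening goes with later progression: HR 0.80 or 0.68, false positives 15% or 35%;
- no relation: HR 1.00, false positives about 4%.

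If patients without a second G8 are counted as not worsened, HR is 1.25 with 18% false positives even when there is no relation. With the clock at progression, or delayed entry at progression, HR is 0.98 to 1.02 with 4–6% false positives in every case.

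**A true effect.** With a true post-progression HR of 2.0 for worsening, unrelated to time to progression, the randomization clock returns about 1.78 and the progression clock about 2.01. With a true HR of 1.10 per point lost, the randomization clock returns 0.99 at a drift of 0.1 and 0.93 to 0.95 at 0.2; the progression clock returns 1.10.

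**The case against.** **The clock is inferred.** The sentence on G8 change names no time origin, risk set or coding. It could mean only that a Cox model and graphs will be used again, and a Cox model of post-progression survival would fit those words. A statistical analysis plan that is not shown may set this out. This stands as a limit on certainty. It does not remove the point, because the article fixes the method by reference to the baseline model and defines no time-to-event outcome with another origin.

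**Inflation of false positives is conditional.** If change is unrelated to time to progression, the null analysis of progressors is unbiased. This stands. A reader might infer that a decline will look protective, but nothing in the article gives the direction of the link, and the simulations move both ways.

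**The immortal-time label is loose.** Among progressors everyone shares the guaranteed survival; what drives the bias is correlation of the covariate with time to progression. Adding linear time to progression to the randomization-clock model brought HR to 1.00 with 6–8% false positives. The planned adjustment for known clinical prognostic factors might include it, but the article does not name it.

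**PFS.** A reader might infer a circular analysis in which G8 change predicts PFS, the event at which it is measured. The article nowhere names PFS as the outcome for G8 change, so this cannot be charged to the plan. It is only worth ruling out.

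**Novelty.** The claim to be first concerns the prognostic role of the G8 score, defined by the split at 14. It is not made for G8 change.

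**Conclusion.** The point holds in a limited form. Taken together, the article's statements most naturally put a covariate measured at progression on a randomization clock. That analysis is biased whenever G8 change is related to time to progression, and it dilutes a true effect even when it is not.

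The size cannot be read from the document. About 40% false positives is an illustration that needs a drift of 0.1 point per month, noise SD 2 and 12-month median post-progression survival; with no drift the excess is nil. The benefit of moving the clock depends far less on these assumptions, since the progression clock stayed near the nominal level in every setting tried.

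Severity is moderate. A reader might infer that trial conclusions are in danger, but secondary analyses are declared descriptive, and the primary endpoint, its test and the sample size are untouched. Confidence is also moderate, because the time origin is inferred.

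**What to change.** Replace the sentence on G8 change with a defined analysis:

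- **Preferred.** Cox model of post-progression survival, with time origin at the progression G8 assessment, in patients alive and assessed then. Include baseline G8 and G8 change, and adjust for time to progression and arm.
- **Alternative.** Keep OS from randomization and enter G8 as a time-dependent covariate that is updated only when the second assessment is made. Add a time-dependent indicator of progression, so that the G8 term does not absorb the effect of progression itself.
- **In either case.** State that PFS is not an outcome for G8 change, and that patients without a second G8 are not coded as unchanged.

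The cost is wording in the analysis plan; no new data or patients are needed. The small downside of the preferred form is that it covers only patients who progressed and were re-assessed, roughly 130 to 144 of 180 under the assumptions above if every progressor is re-assessed, so its result applies to them and not to all randomized patients.

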### Safety

All adverse events are recorded under the responsibility of the investigator in the subjects’ medical records and in electronic Case Report Forms (eCRFs), severity and relationship with the study treatment is assessed. Any medical condition that at the judgment of the Investigator may affect patients’ safety is a possible reason for treatment discontinuation.

An adverse event with the following characteristics: fatal, life threatening, requiring in-patient hospitalization or prolongation of existing hospitalization; resulting in persistent or significant disability/incapacity; congenital anomaly/birth defect or other significant medical hazard is defined as serious adverse event (SAE) and must be reported to the coordinating center within 24 h from its occurrence. The investigator should notify the Sponsor of all SAEs in accordance with local procedures, statutes and the European Clinical Trial Directive (where applicable). The Sponsor is responsible for the medical review of all SAEs and for their notification to the appropriate Ethics Committees, Competent Authorities and participating Investigators, in accordance with local requirements and the European Clinical Trial Directive.

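### The CRASH–toxicity analysis stops at grade 4, so a patient whose only severe event was fatal counts as free of severe toxicity; a trend test should be added beside the chi-square (minor)

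*Protocol article*

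**What the plan says.** Under *Statistical design* the protocol article fixes both the outcome and the test: "The association of CRASH score with toxicity will be assessed comparing G3–4 adverse events in the four risk categories", and these categories are compared as "low, medium-low, medium-high and high risk) by means of chi-square test".

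Four other places bear on this:

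- *Geriatric assessment*, on the purpose of CRASH: "This score stratifies patients in four risk categories of severe hematologic, non-hematologic and combined toxicities".
- *Study endpoints* lists the categories in rising order ("four categories of different toxicity risk (low, medium-low, medium-high, high), will be prospectively correlated with toxicity") and grades events by the "Common Terminology Criteria for Adverse Events (NCI CTCAE) version 4.0".
- *Safety* foresees fatal events in its definition of a serious adverse event: "An adverse event with the following characteristics: fatal, life threatening".
- The CRASH scoring table (Table 3) gives the chemotherapy-risk item 0 points in arm B and 1 point in arm A.

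*Statistical design* also labels the secondary analyses descriptive. It gives no power, error rate, toxicity rates or category sizes for the CRASH analysis.

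**The concern.** There are two parts, of unequal weight.

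**Outcome.** CTCAE assigns grade 5 to a death from an adverse event. A range that ends at grade 4 leaves that death out. If the patient had no separate grade 3–4 event, the patient enters the table as a non-event. The Discussion says the scores will be related to severe treatment-related toxicity, and the outcome as written is narrower than that. If fatal cases fall mainly in the higher-risk categories, leaving them out flattens the gradient that the analysis is meant to show.

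**Test.** The categories run from low to high risk, and the clinical question is whether toxicity rises along them. A chi-square test over four categories is normally read as Pearson's test on 3 degrees of freedom, which ignores the order. For a steady gradient, that costs power.

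**Working it through.** **1. The plan's own figures.** No power is stated for the CRASH analysis. The only power figure is 90% for the primary test with 90 patients per arm. On the survival-probability scale (6-month PFS 0.50 against 0.65, one-sided 5%) it reproduces:

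Φ[(0.15 − 1.645·√(0.25/90)) / √(0.65·0.35/90)] = 0.896.

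This has no bearing on CRASH. The input needed from the plan is N = 2 × 90 = 180. All toxicity rates and category shares below are assumptions.

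**2. Who is misclassified.** The text does not state the unit of analysis. Taking it as the patient:

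| Patient's severe events | G3–4 as written | Grade 3 or higher |
|---|---|---|
| Grade 3–4 only | event | event |
| Grade 3–4 and a fatal event | event | event |
| Fatal event only | **non-event** | event |
| None | non-event | non-event |

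Only the third row changes. At an assumed 1–3% fatal toxicity, all fatal cases together number 180 × 0.01 = 1.8 to 180 × 0.03 = 5.4. The third row is a subset of these.

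**3. What the omission could do.** Assume equal quarters, true rates (grade 5 included) of 40/49/58/67%, and fatal-only cases of 0/1/2/4% across the categories. That is a mean of 1.75%, or 180 × 0.0175 ≈ 3 patients. The rates as written become 40/48/56/63%. With the formulas in step 4, power falls from 61% to 47% (Pearson) and from 77% to 64% (trend). This is an adverse illustration: it needs the deaths to concentrate in the upper categories and none of these patients to have a grade 3–4 event.

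**4. Pearson against trend.** With shares wᵢ, rates pᵢ, mean rate p̄ and scores xᵢ = 0, 1, 2, 3, the noncentralities are

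- Pearson, 3 df: λ₃ = N·Σwᵢ(pᵢ − p̄)² / [p̄(1 − p̄)]
- Trend, 1 df: λ₁ = N·[Σwᵢ(xᵢ − x̄)(pᵢ − p̄)]² / [Σwᵢ(xᵢ − x̄)²·p̄(1 − p̄)]

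Power is the noncentral chi-square probability of exceeding 7.815 (3 df) or 3.841 (1 df), at 5%.

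Example: equal quarters, 40/50/60/70%. Then p̄ = 0.55 and Σwᵢ(pᵢ − p̄)² = 0.0125, so λ₃ = 180 × 0.0125/0.2475 = 9.09. For the trend, 0.125²/1.25 = 0.0125, so λ₁ is also 9.09. The same signal is spread over 3 df or concentrated in 1.

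| Shares (%) | Rates (%) | Pearson | Trend | Difference |
|---|---|---|---|---|
| 25/25/25/25 | 40/50/60/70 | 71.6% | 85.4% | +13.8 |
| 25/25/25/25 | 40/47.5/55/62.5 | 44.6% | 61.4% | +16.8 |
| 25/25/25/25 | 50/55/60/65 | 21.7% | 32.9% | +11.2 |
| 10/40/40/10 | 40/50/60/70 | 41.9% | 58.5% | +16.6 |
| 10/40/40/10 | 50/55/60/65 | 13.0% | 19.4% | +6.4 |
| 25/25/25/25 | 40/40/60/60 | 60.3% | 67.0% | +6.7 |
| 25/35/30/10 | 35/55/55/55 | 47.2% | 42.9% | −4.3 |
| 25/35/30/10 | 45/45/45/80 | 65.1% | 41.5% | −23.6 |
| 25/25/25/25 | 40/60/40/60 | 60.3% | 22.4% | −37.9 |

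For an exactly linear gradient, 80% power needs λ = 10.90 on 3 df and 7.85 on 1 df, so Pearson needs 10.90/7.85 = 1.39 times the patients.

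**5. Stratifying by arm.** Arm contributes a point to CRASH, so the category mix differs between arms by construction. Simulations with assumed shifts show both sides:

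- *Against stratifying.* With shares of 40/35/20/5% in one arm and 10/35/40/15% in the other, the arm-stratified trend test has about 66% power for rates of 35/45/55/65%. With no shift (shares 25/35/30/10%) it has about 72%. For 40/40/60/60% with the shift it has about 57%, against 59% for the pooled Pearson test.
- *For stratifying.* With shares of 35/35/22/8% in arm B and 15/35/35/15% in arm A, an arm odds ratio of 2 and no other CRASH effect, the pooled test rejects in 6.8% of trials and the stratified trend in 5.1%.

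**The case against.** The strongest reply is that this is one descriptive secondary analysis. No sample size or error rate rests on it, and an unordered chi-square is a valid test of association. The text says only chi-square, which does not rule out a chi-square for trend. The grade range may be shorthand in a condensed article, and fatal events are reported as serious adverse events in any case.

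Most of this stands, and it sets the severity. It does not remove the outcome point: the article states a grade range, the range ends at 4, and reporting deaths as serious adverse events does not put them into the CRASH table.

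Three stronger readings are tempting, and the document does not support them:

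- *Every fatal toxicity is scored as no severe toxicity.* On a per-patient count, this is true only where no grade 3–4 event was recorded.
- *The high-risk group's rate would be badly distorted.* Two misclassified deaths among 18 high-risk patients would lower its rate by 2/18 = 11 percentage points. But both numbers are invented, and the article gives no fatality rate and no distribution of deaths by category.
- *The chi-square is wrong and an arm-stratified Mantel trend test should replace it.* The trend test loses for non-monotone patterns and also for some monotone threshold patterns, including an excess confined to the high-risk group. Stratifying by arm removes the part of the score that comes from the arm item, and so changes the question.

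**Conclusion.** The outcome definition should be corrected. As written it can count a fatal-only case as free of severe toxicity, which does not fit the stated purpose of CRASH. Few patients are likely to be affected, and any bias toward no association depends on such cases falling in the higher-risk categories.

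A trend test is a worthwhile addition for ordered categories. Its gain is about 11–17 points in the three equal-quarter linear gradients. It is smaller for the equal-quarter step pattern and for the shallow gradient with uneven shares, and it turns into a loss in the last three patterns tabulated. All these figures rest on assumed rates and shares. They support adding the test and do not support dropping Pearson.

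Severity: minor. The analysis is secondary and descriptive, and the primary PFS analysis is unaffected.

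**What to change.** 1. Define the CRASH toxicity outcome per patient as worst CTCAE grade 3 or higher (grades 3–5).
2. Report the rate with a confidence interval in each of the four categories.
3. Add a Cochran-Armitage trend test with scores 0–3, and keep the Pearson chi-square alongside it. Name both in advance so that neither is chosen after seeing the pattern.
4. Give an arm-stratified trend test as a sensitivity analysis, noting that arm is one of the CRASH items.

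Cost: a change of wording in the analysis plan. No new data are needed, because all adverse events and their severity are already recorded. The drawback is two tests that may disagree; the category rates then show which pattern lies behind the disagreement.
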